## Abstract

Binge-eating disorder (BED) is a psychiatric disorder characterized by recurrent episodes of eating a large amount of food in a discrete period of time while experiencing a loss of control. Cognitive behavioral therapy-enhanced (CBT-E) is a recommended treatment for binge-eating disorder and is typically offered through 20 sessions. Although binge-eating disorder is highly responsive to CBT-E, the cost of treating these patients is high. Therefore, it is crucial to evaluate the efficacy of low-intensity and low-cost treatments for binge-eating disorder that can be offered as a first line of treatment and be widely disseminated. The proposed noninferiority randomized controlled trial aims to determine the efficacy of web-based guided self-help CBT-E compared to treatment-as-usual CBT-E. Guided self-help will be based on a self-help program to stop binge eating, will be shorter in duration and lower intensity, and will require fewer therapist hours. Patients with binge-eating disorder (N = 180) will be randomly assigned to receive guided self-help or treatment-as-usual. Assessments will take place at baseline, mid-treatment, at the end of treatment, and at 20- and 40-weeks post-treatment. Treatment efficacy will be measured by examining the reduction in binge-eating days in the previous 28 days between baseline and the end of treatment between groups, with a noninferiority margin (Δ) of 1 binge-eating day. Secondary outcomes will include full remission, body shape dissatisfaction, therapeutic alliance, clinical impairment, health-related quality of life, attrition, and an economic evaluation to assess cost-effectiveness and cost-utility. The moderators examined will be baseline scores, demographic variables, and body mass index. It is expected that guided self-help is noninferior in efficacy compared to treatment-as-usual. The proposed study will be the first to directly compare the efficacy and economically evaluate a low-intensity and low-cost binge-eating disorder treatment compared to treatment-as-usual. If guided self-help is noninferior to treatment-as-usual in efficacy, it can be widely disseminated and used as a first line of treatment for patients with binge-eating disorder. The Dutch trial register number is R21.016. The study has been approved by the Medical Research Ethics Committees United on May 25th, 2021, case number NL76368.100.21.

## Introduction

1

Binge-eating disorder (BED) is a serious psychiatric disorder with detrimental effects on physical and mental health. Patients with BED engage in recurrent episodes of eating abnormally large amounts of food in discrete periods of time while feeling a lack of control over their actions (1). Patients with BED frequently eat until they are uncomfortably full and experience elevated levels of distress around their behavior (1). The *Diagnostic and Statistical Manual of Mental Disorders – 5^th^ Edition* (2) states that for a diagnosis of BED, binge eating must occur at least one day per week for three months, and the binges must not be associated with compensatory behaviors such as self-induced vomiting, excessive exercise, or fasting. BED is more common than anorexia nervosa and bulimia nervosa combined (3), with a lifetime prevalence of 1.9% in upper- and high-income countries (4, 5), however the actual prevalence of BED is likely much higher given many individuals who meet BED criteria never get a formal diagnosis or receive treatment (6). Approximately 30% of patients with BED have excess weight, and 32% are classified as having obesity (classes 1 – 3), resulting in many serious health conditions (4).

Many BED patients have secondary health complications including type II diabetes, hypertension, dyslipidemia, heart disease, and stroke (4, 7). Psychiatric comorbidities are seen in up to 80% of patients with BED, with many patients having increased rates of anxiety disorders, major depressive disorder, obsessive-compulsive disorder, and bipolar I and II (8). Patients with BED also score poorer on quality of life measures due to excess weight and higher levels of depression and anxiety (9).

The impact of BED on healthcare utilization is significant; many patients with BED receive inappropriate care through weight-loss programs and engage in treatments aimed at addressing their psychological comorbidities (4, 10) rather than their eating disorder as the root problem. The economic cost of BED is substantial; in the United States, the one-year general healthcare cost for those with BED was $18,152 higher than those without an eating disorder (in estimated 2014 USD; 11). Another study from the USA found that people with BED have higher generic healthcare costs by approximately $2,758 per year compared with their age- and gender-matched means (in estimated 2009 USD; 12). In the UK, the yearly cost of health services per eating disorder patient is £8,850, with an additional £19,700 in direct and indirect financial costs to patients and their caregivers (13). Such figures are unknown for Dutch patients and caregivers; however, these figures are likely similar in the Netherlands, highlighting the need for effective, efficient, and low-cost treatments for BED.

Cognitive behavioral therapy-enhanced (CBT-E; 14), is an evidence-based treatment for BED (15–17). CBT-E uses a transdiagnostic approach for the treatment of eating disorders and takes a highly individualized approach (12). The treatment is broken down into four stages to strategically address disturbances in eating behaviors, establish a normalized eating pattern, and promote new ways of coping (12). CBT for eating disorders can be delivered in person, through guided self-help (18–22) or self-help with minimal support and guidance from a therapist (23), video conferencing (24), or a recently developed web-based GSH program (21, 25). Given CBT has several methods of delivery, it is important to evaluate whether a stepped-care model (e.g. providing patients with low-cost and low-intensity treatment first before referring to specialized or more intensive care) is feasible, whereby less-intensive treatments such as web-based GSH are offered as a first-line of treatment (16).

The stepped-care model, or firstly referring patients for low-intensive care and increasing the level of care as needed, is ideal from an economic and healthcare perspective, as it can decrease the need for costly and specialized services, reduce treatment waiting times compared with more conventional treatments (26), and may improve long-term patient outcomes (27, 28). The stepped-care model is also preferable for patients as there is less social disruption, less or no need to take time off from school or work, geographical barriers are removed, and patients can have increased autonomy (29, 30). The stepped-care model is recommended for BED in the United Kingdom and Australia, whereby GSH is recommended as the first line of treatment (15, 16). However, despite the potential cost savings in the Netherlands (21, 31, 32) and long waiting lists for treatment, the Netherlands continues to recommend in-person therapy as a first line of treatment (33). Therefore, it is critical to examine whether a lower-intensity and remotely accessible treatments such as GSH and web-based GSH are viable for patients with BED. If GSH is offered as a first line of treatment, patients will benefit from shorter waitlists, improved health and quality of life, and the healthcare burden from BED can be mitigated (34, 35).

The first version of CBT-E self-help was developed by Christopher Fairburn (18, 36) in the book *Overcoming Binge Eating*, a self-help book comprised of two parts: Part I offers a description of binge eating and why it occurs, and Part II provides a CBT-E-based self-help program to stop binge eating. The book is intended for anyone with a binge-eating problem, as long as they are not significantly underweight (36). Studies have suggested GSH can empower patients to take ownership and accountability over their eating disorder recovery (37, 38), leading to a more robust recovery. Furthermore, a review on self-help and GSH for eating disorders suggests that patients using these modalities learn to manage binge eating without relying on external supports, which may better support them in the long-term to handle setbacks. If patients learn and develop the skills that they need to manage their binge eating on their own without relying on external supports, they may be better equipped to handle setbacks (37). A recent randomized controlled trial comparing web-based GSH CBT-E with a waitlist condition found that the treatment reduced the number of objective binges from an average of 19 (*SD* = 16) at the start-of-treatment to 3 (*SD* = 5) at the end of treatment, with an interaction effect between time and condition (treatment or waitlist; *F2*,178 = 18.55; *P*<.001) (21). These improvements were sustained at 12- and 24-week follow-ups (21). These findings highlight the importance of not only GSH, but remotely accessible GSH treatments for BED, which could be offered to patients who lack access to treatment or do not have a formal diagnosis, While web-based GSH CBT-E offers many advantages, it is unknown whether it is as efficacious as treatment as usual CBT-E. This is critical in determining whether web-based GSH is a viable alternative that can be offered as a first line of treatment for BED.

The present study aims to determine whether web-based GSH CBT-E is noninferior in efficacy compared to treatment as usual CBT-E (TAU CBT-E) for treating BED. Efficacy will be examined by the reduction of binge-eating days, defined as the number of days on which one or more binge-eating episodes occurred, at the end of treatment. This study sought to determine whether web-based GSH CBT-E is noninferior in efficacy compared to TAU CBT-E in reducing the number of binge-eating days at the end of treatment. In addition to examining the reduction in binge-eating days, several secondary outcomes will also be evaluated, including full remission, body shape dissatisfaction, therapeutic alliance, clinical impairment, health-related quality of life, attrition, and an economic evaluation to assess the cost-effectiveness and cost-utility of web-based GSH CBT-E compared to TAU CBT-E (described below). Moderators will be examined, including baseline scores, demographic variables, and body mass index (BMI). It is expected that participants in both groups will have a reduction in the number of binge-eating days, with web-based GSH CBT-E being noninferior to TAU CBT-E.

## Method

2

### Trial design

2.1

A randomized controlled trial will be conducted comparing the efficacy and noninferiority of a 12-week, web-based GSH CBT-E with the standard 20-week TAU CBT-E for BED at a specialized center for the treatment of eating disorders in the Netherlands (Novarum). Both treatments will be based on the CBT-E treatment protocol and are web-based. Assessments will take place at baseline (before randomization) and at four timepoints during and after treatment. Because the treatments vary in length, assessments will be synchronous in treatment phase rather than in the number of weeks since baseline. Web-based GSH CBT-E assessments will begin at the start of treatment (week 0), mid-treatment (week 5), end of treatment (week 12), 20 weeks post-treatment (week 32), and 40 weeks post-treatment (week 52). TAU CBT-E assessments will begin at the start of treatment (week 0), mid-treatment (week 5), end of treatment (week 20), 20 weeks post-treatment (week 40), and 40 weeks post-treatment (week 60; see **Table 1** for the breakdown of assessment timing). The duration of treatment and assessments in this study is 52 weeks for GSH and 60 weeks for TAU, making the total time horizon of the study 60 weeks (14 months). The study will be performed in line with the updated CONSORT guidelines for reporting parallel group randomized trials (39). To examine the cost-effectiveness and cost-utility of the web-based GSH CBT-E and TAU CBT-E, a complete economic evaluation will be conducted using ISPOR and CHEERS guidelines (40, 41). This study has been approved by the Medical Ethical Committee-United.

**Table 1 T1:** Timing of planned assessments between groups.

	Weeks from baseline assessment	
Treatment group	GSH	TAU
T0: Baseline assessment	week 0	week 0
T1: Mid-treatment evaluation	week 5	week 5
T2: End of treatment	week 12	week 20
T3: 20 weeks post-treatment	week 32	week 40
T4: 40 weeks post-treatment	week 52	week 60

### Participants

2.2

#### Eligibility criteria

2.2.1

Participants must have a referral from their general practitioner, a DSM-5 diagnosis of BED or Other Specified Feeding and Eating Disorder – BED subtype (BED of subthreshold frequency and/or duration) as assessed by a psychiatrist or clinical psychologist, be ≥ 18 years, have a BMI between 19.5 kg/m^2^ ≤ 40 kg/m^2^, be sufficiently proficient in Dutch, have internet access and a computer or tablet, and provided informed consent to participate in the study. If a participant chooses to not participate in the study, they will be offered TAU CBT-E. Participants will be excluded if they have an eating disorder other than BED/Other Specified Feeding and Eating Disorder – BED subtype, acute psychosis, major depressive disorder, or suicidal ideation, as assessed via the Structural Clinical interview DSM-5 (SCID-5; 40, 42), have undergone any eating disorder treatment/intervention in the 6 months prior to their assessment, are pregnant, use recreational drugs (ex. marijuana, ecstasy) or take any medication that might influence eating behavior such as stimulant medications (ex. lisdexamphetamine), chlorpromazine, lithium, or olanzapine.

#### Recruitment

2.2.2

Participants will be recruited from a Dutch eating disorder treatment center. Eligible patients will receive written and verbal study information and an informed consent form that will explain the research goals and provide information about their participation in the study. Patients will have two weeks to decide whether they want to participate in the study, during which time they can ask any questions they have regarding the study. Once an informed consent form has been signed and received, a phone appointment will be scheduled to conduct the baseline assessment. Participants will be informed that they can discontinue the study for any reason and at any time. To promote participant retention and follow-up, participants will be encouraged to contact the lead researcher or their therapist if they have any concerns, and they will receive a €20 gift card after completion of the final posttreatment assessment (week 40).

### Interventions

2.3

#### Therapists

2.3.1

All therapists are specialized in CBT-E treatment for eating disorders, have completed training by the Centre for Research on Eating Disorders at Oxford (CREDO), and have read *Overcoming Binge Eating* (36). To ensure a thorough understanding and adherence of administering web-based GSH CBT-E and TAU CBT-E, therapists will complete a two-day workshop and attend weekly 45-minute supervision sessions by the project leader ([name]) to ensure adherence to treatment plans and research protocols.

#### Treatment as usual CBT-E

2.3.2

Treatment as usual CBT-E is the focused version of CBT-E, as it is indicated for patients with BED and exclusively addresses eating disorder pathology and is more effective than the broad version, which addresses external mechanisms (14). During the COVID-19 pandemic, face-to-face CBT-E treatment for BED could no longer continue, and consequently, video conferencing CBT-E was introduced as TAU at Novarum to ensure continued patient care. In this study, TAU CBT-E will be delivered through video conferencing over 20 sessions, each 50 minutes in length. The treatment follows the same structure and duration as face-to-face CBT-E; however, it is offered completely remotely. Video conferencing CBT-E has been as effective as face-to-face treatment (27, 31, 43, 44). Participants receiving TAU CBT-E will be required to monitor their eating behaviors, weigh themselves regularly, evaluate their progress, find alternative activities to binge eating, improve their problem-solving skills, plan for relapse prevention, and learn ways to cope through setbacks (36).

#### Web-based guided self-help CBT-E

2.3.3

Web-based guided self-help CBT-E is an adapted and brief version of the focused form of CBT-E. The treatment is based on the guided self-help book *Overcoming Binge Eating* (36) is also available in Dutch *Overwin je eetbuien, waarom je te veel eet en hoe je daar mee kunt stoppen* (43), and is being built into a Dutch online application (Karify by Avinty). Before beginning web-based GSH, participants will be required to read part 1 of *Overcoming Binge Eating* (44). Treatment will be offered completely remotely using the web-based application, and focus on the same CBT-E principles as in TAU: monitoring eating behaviors, regular weighing, evaluating progress, finding alternative activities to binge eating, and improving problem-solving skills (36). Participants will receive weekly scripted feedback from a therapist during 12 phone sessions of 20 minutes. During these calls, therapists will review past assignments and discuss next steps in treatment.

### Outcomes

2.4

#### Primary outcome

2.4.1

The primary outcome will be the reduction in the number of binge-eating days in the previous 28 days between baseline and the end-of-treatment between groups. Binge-eating days will be defined as days on which one or more binge-eating episodes occurred, as reported by each participant. The primary outcome will be measured at the end of treatment.

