#### Sample size and power estimation

2.5.1

The primary objective of the proposed study is to determine whether GSH is noninferior to TAU in efficacy. It is expected that both groups will have a reduction in the number of binge-eating days, and GSH is expected to be noninferior compared to TAU in the reduction of binge-eating days in the previous 28 days at the end of treatment.

To calculate the sample size for this noninferiority trial, the significance level was set at *α* = 0.05, power was aimed at 80%, and the noninferiority margin (*Δ*) was set to 1 (*SD* = 2.4) binge-eating day (68) in the previous 28 days between groups. With these assumptions, *n* = 144 (*n* = 72 per arm) participants will be needed to determine noninferiority. The noninferiority margin and standard deviation are based on noninferiority margins from prior studies examining online treatments to reduce eating disorder behaviors (68, 69) and clinical experts on BED treatment outcomes. Efficacy studies of CBT-E (70) and internet-based guided self-help for BED (68) report a 20% dropout; therefore, 20% more participants will be included to compensate for dropout. The sample size corrected for dropout is *N* = 180 (*n* = 90 per arm); therefore 180 participants will be randomized. This sample size calculation was performed using the R package ‘SampleSize4ClinicalTrials’ (71–73) based on a continuous outcome, noninferiority design.

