#### Statistical analyses

2.5.3

To measure the efficacy of treatment on the reduction of binge-eating days, the number of binge-eating days will be reported as means (standard deviation) between groups and analyzed using a general linear mixed model. Effect sizes will be calculated using Cohen’s *d* (0.2 small, 0.5 medium, 0.8 large; 74) and adjusted for bias (75). Sensitivity analyses will be conducted to test the robustness of the results; given the 20% anticipated dropout rate, analyses will be run on an intention-to-treat protocol, and multiple imputations will be used to handle missing data. To examine possible treatment moderators, a regression analysis with subgroups will be performed by analyzing interaction terms between the moderators and treatment group. Data will be nested within BMI groups (19.5 ≤ 35 and 35.1 ≤ 40) and include random and fixed effects. If significant interactions exist, *post-hoc* analyses will be performed to further explore the moderation.

The cost-effectiveness and cost-utility analyses will be performed from a healthcare perspective. The cost-effectiveness analysis will examine the reduction in binge-eating days as the measure of effect measure, and the cost-utility analysis will use QALYs as effect measure. Differences in costs and effects between groups will be calculated as the difference in cumulative direct costs using the reduction of binge-eating days as the outcome measure. ICERs will be calculated as ICER = (Costs GSH − Costs TAU)/(Effects GSH – Effects TAU) with reduction in binge-eating days as the effect. ICERs to report comparative differences in QALYs will be calculated as ICER = (Costs GSH − Costs TAU)/(Effects GSH – Effects TAU). The costs, effects, and ICERs will be plotted on a cost-effectiveness plane to demonstrate the differences between the costs and effects of both groups, with TAU positioned at the origin of the cost-effectiveness plane. Cost-effectiveness acceptability curves will be used to examine the probability that the cost-effectiveness of GSH is equally as effective with lower costs compared to TAU by a willingness-to-pay for each unit of effect (reduction in binge-eating days or QALYs). The willingness-to-pay for each additional unit of effect in the Netherlands ranges between €20,000 and €80,000 per QALY (25, 76) and €22–€110 per binge-free day in the United Kingdom and the United States (31). All statistical analyses will be conducted using R (77) and SPSS (78).

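### The primary outcome is a change from baseline and no baseline adjustment is stated for the primary comparison; adding it would be a free gain in precision

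*Protocol article*

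**What the plan says.** Protocol article, Primary outcome: "The primary outcome will be the reduction in the number of binge-eating days in the previous 28 days between baseline and the end-of-treatment". Sample size and power estimation and Anticipated results both put noninferiority on the difference in reduction between arms, against 1 day.

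Protocol article, Statistical analyses: "the number of binge-eating days will be reported as means (standard deviation) between groups and analyzed using a general linear mixed model". This sentence does not say whether baseline is a covariate, one of the repeated responses, or constrained equal across arms. Baseline scores (objective binges, eating disorder severity) appear under Secondary outcomes, Moderators and Statistical analyses only as candidate moderators, that is, in interaction with treatment.

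Two places bear on the variance. The Introduction cites a waitlist-controlled trial of web-based guided self-help with a fall in "the number of objective binges from an average of 19 (*SD* = 16) at the start-of-treatment to 3 (*SD* = 5"); the unit there is episodes. The sample-size section says "the noninferiority margin (*Δ*) was set to 1 (*SD* = 2.4) binge-eating day", without saying whether 2.4 is the SD of the change, of the end-of-treatment value, or a residual SD.

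**The concern.** The outcome and the hypothesis are both worded as a difference in reduction, and baseline is given no role in the primary comparison. A natural way to carry this out is a mixed model with T0 among the responses and a group-by-time contrast from T0 to T2. With complete data that contrast is the difference in mean raw change, so chance imbalance at baseline passes into the estimate with a coefficient fixed at 1. Baseline adjustment estimates that coefficient instead.

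Noninferiority against a 1-day margin turns on the width of the confidence interval. Because allocation is randomized, baseline adjustment targets the same difference in mean reduction, so the margin keeps its meaning. Precision would be given up for nothing in return.

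**Working it through.** **The plan's own figure.** Inputs from the sample-size section: margin 1, SD 2.4, α = 0.05, power 80%; assumed true difference 0. Taking α one-sided, n per arm = 2(1.645 + 0.842)² × 2.4² / 1² = 71.2, so 72 per arm and 144 in total; 144 / 0.8 = 180. The stated numbers reproduce. They do not show which SD 2.4 is.

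**Formulas.** Let s0 and s1 be the baseline and end-of-treatment SDs and r their correlation, taken as common to both arms.

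- Unadjusted change: V_c = s0² + s1² − 2·r·s0·s1
- Baseline-adjusted: V_a = s1²(1 − r²)
- V_c − V_a = (s0 − r·s1)², which is never negative, so raw change is never more precise.
- V_c > s1² when s0 > 2r·s1. Raw change is then noisier than comparing end-of-treatment values and ignoring baseline.
- Information lost = 1 − V_a/V_c, which depends only on s0/s1 and r.

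**The only SD pair in the article (16 and 5, episodes).** The correlation is not given and is assumed.

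| r | V_c | V_a | SD of change | adjusted SD | V_c/V_a |
|---|---|---|---|---|---|
| 0 | 281 | 25.00 | 16.8 | 5.0 | 11.2 |
| 0.3 | 233 | 22.75 | 15.3 | 4.8 | 10.2 |
| 0.5 | 201 | 18.75 | 14.2 | 4.3 | 10.7 |
| 0.7 | 169 | 12.75 | 13.0 | 3.6 | 13.3 |

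At r = 0.3 the SD of change (15.3) is also about three times the end-of-treatment SD (5).

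**Binge-eating days.** The article gives no baseline and end-of-treatment SDs, so these pairs are assumptions, with r from 0 to 0.7.

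| s0, s1 (days) | information lost |
|---|---|
| 5, 5 | 15% to 50% |
| 6, 5 | 33% to 59% |
| 6, 4 | 56% to 69% |
| 8, 5 | 61% to 72% |
| 6, 2.4 | 84% to 86% |

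Examples: for (5, 5) at r = 0.7, V_c = 50 − 35 = 15 and V_a = 25 × 0.51 = 12.75, a loss of 15%. For (6, 2.4) at r = 0, V_c = 36 + 5.76 = 41.76 and V_a = 5.76, a loss of 86%. The most extreme combination of these SDs, 8 with 2.4, goes further: at r = 0, 1 − 5.76/69.76 = 92%. If the baseline SD were below the end-of-treatment SD the loss could fall below 15%; it is zero at s0 = r·s1.

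**If 2.4 is the SD of change.** Then s0 cannot exceed 2.4/√(1 − r²), which is 2.4 at r = 0 and 3.4 at r = 0.7, so the assumed SDs in the table would be too large. Their ratios can still be used. With equal variances the adjusted SD is 2.4 × √((1 + r)/2), that is 1.70 at r = 0 and 2.21 at r = 0.7, and the loss is again 15% to 50%.

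**Does defining the outcome as a reduction cost precision in itself?** No. With baseline as a covariate, analysing the change and analysing the end-of-treatment value give the same treatment effect; in a simulated check with 72 per arm they differed by at most about 3 × 10⁻¹⁴. The choice that matters is adjusted or unadjusted.

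**The case against.** The strongest reply is that the article nowhere specifies an unadjusted analysis. The outcome sentence defines a variable, not an estimator, and the analysis sentence names a mixed model on binge-eating days that could perfectly well contain baseline as a covariate. Model terms are ordinary content of a statistical analysis plan, and a journal article condenses. This stands: a reader might infer that the plan commits to a raw change comparison, and the text does not say so.

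Second, the 16 and 5 are for objective binge episodes in another trial. Episodes are unbounded, whereas binge-eating days are capped at 28, so the ratio need not carry over. This stands too. A reader might infer that most of the precision would be lost; on part of the assumed day-scale range the loss is below half.

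Third, a reader might infer that the trial is underpowered. That depends on which SD 2.4 is and whether it is realistic, which is a separate question. If it is the SD of change, the planned sample size holds and adjustment only adds precision.

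Fourth, equality with the raw-change contrast holds for complete data, while the plan expects 20% dropout. That limits how exact the equality is, but not the direction of the comparison.

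What remains is that the outcome and hypothesis are fixed as a difference in reduction, baseline is given a role only as a moderator, and a better method is available from data already collected.

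**Conclusion.** The point holds as a free improvement. The primary outcome is a change from baseline, and the primary comparison as described names no baseline adjustment. If it were run as an unconstrained group-by-time contrast, it could not be more precise than an adjusted analysis, and it would usually be less so. The cost cannot be fixed from the article: about a 10-fold variance ratio on the episode SDs, and about 15% to 86% of the information over the day-scale pairs tabulated. The day-scale figures rest on assumed SDs and on assumed correlations of 0 to 0.7. The article does not support saying that the analysis is unadjusted, that most of the precision is lost, or that power falls to any particular value.

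**What to change.** State that the primary estimate is GSH minus TAU in binge-eating days at T2, from the mixed model with group, visit and group-by-visit terms and with baseline binge-eating days and BMI stratum as fixed covariates. Alternatively, keep T0 as a response and constrain the baseline means to be equal across arms. The constrained form keeps every randomized patient with a baseline value in the likelihood, including those with no later visit, who drop out of the covariate form unless imputed; it therefore fits the intention-to-treat aim better. Compare the upper confidence limit of this contrast with 1 day, and report the raw mean reductions descriptively. It would help to say in the same place which SD the 2.4 represents.

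The cost is a few lines of analysis-plan wording, settled before the data are analysed. Binge eating is already assessed at T0 and BMI group is already the randomization stratum. The estimand, the margin and the sample size stay as they are.
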